### Recruitment and Consent Procedures

#### Screening

Recruitment will take place between November 2020 and November 2021, with the aim of including all eligible patients receiving medicinal cannabis at participating sites during the recruitment period. Figure 1 provides an overview of the patient recruitment and data collection procedures.

**Figure 1 figure1:**
[figure not shown]
Patient recruitment and data collection process.

LGP, following the World Health Organization Guidelines on Good Agricultural and Collection Practices for Medicinal Plants and European Union-Goods Manufacturing Practices standards, provides its medicinal cannabis products in Australia under the SAS. As part of this process, LGP engages with medical cannabis–focused clinics, authorized prescribers, and other health care professionals prescribing LGP products and will be responsible for identifying recruitment sites for this study. Advertising and information relevant to the study will be disseminated via a dedicated study website and social media platforms. Content on the study website will inform potential participants and recruitment sites of the study objectives, terms, and conditions, including eligibility criteria, and who to contact for more information. Approved recruitment sites will receive study-specific training from the University of Sydney researchers regarding participant screening and recruitment.

Patients from participating centers who meet the eligibility criteria will be invited to participate in the study. Patients will be identified by physicians at recruitment sites and approached to participate by either the physician or site staff. A record of those identified as eligible and invited to participate will be logged in the web-based research database with the patient’s verbal consent. Physicians at recruitment sites will use a generic link to access the study database to create a new record for each patient screened.

The physician or staff at recruitment sites will ask if the patient agrees to have the Participant Information Statement and invitation sent to them through email. Patients will be informed that the process involves recruitment site staff entering the information, as per the *Registration and Clinical Data* section, into the research database, which then sends an invitation to them automatically. Participants will be informed that email addresses are stored within the Research Electronic Data Capture (REDCap) system and used solely for sending reminders to complete questionnaires at scheduled time points. REDCap [54] is a secure web-based application developed by Vanderbilt University that runs on the servers of the University of Sydney, ensuring that the data stay within the Sydney University data center.

All patients who provide their email address to receive an invitation for the study will receive their medicinal cannabis product at a standardized cost. As medicinal cannabis is still an unregistered product, it has been difficult to control the cost of the product; consequently, there has been considerable variability in what people pay for the product. LGP has partnered with several pharmacies across Australia to ensure that all participants taking part in this study will be charged the same amount for their product, eliminating variability in out-of-pocket costs and enabling a health economic evaluation.

As soon as an email address is entered in the web-based database, the patient will receive an email invitation with a link to the web-based forms for their record. The email will include the Participant Information Statement (Multimedia Appendix 1) to be considered before giving consent on the web. The Participant Information Statement contains detailed information about the rationale, design, and personal implications of the study. Patients will then provide their consent to join the study by checking the consent box before being able to proceed to the data collection forms or they can opt out of study participation at this point. They have as much time as they need to consider their participation. The patient’s right to refuse consent without giving reasons will be respected. If the patient does not respond to the invitation, 2 daily follow-up reminders will be sent via email, after which the system will automatically record the patient as having selected *opt out* without reason.

Participants will remain free to withdraw from the study at any time without giving reasons and without prejudicing any further treatment. Participants can withdraw responses from the study before the data have been analyzed; otherwise, they will be included.

#### Registration

When physicians at recruitment sites complete the web-based screening form, REDCap will automatically generate a number to be used as the participant’s study ID number for study registration.

#### Data Collection and Assessment

Study data will be recorded by physicians at recruitment sites on case report forms and by participants in the questionnaire booklets. These will be completed on the web through the University of Sydney research data capture system, REDCap [54].

Screening and registration and clinical data will be completed by the physician at the recruitment sites. The REDCap database will collect information only identifiable by REDCap-assigned study record ID numbers. Physicians at recruitment sites will maintain a record of participants’ study ID numbers for each screened and registered participant entered. Where required, data can be updated for individual participants by notifying the study project manager of the corresponding study ID numbers (eg, to record participant withdrawal). If 2 consecutive assessments are missed by participants, the study project manager will contact the physician at the recruitment site to determine the reasons for missed assessments, if known.

#### Registration and Clinical Data

The following patient screening details will be entered into the REDCap web-based registration form by physicians at recruitment sites: age, sex, country, email address, health indications for accessing medicinal cannabis, neuropathic pain screening using the short-form Douleur Neuropathique en 4 Questions [55,56] (if pain is selected as a health indication), duration of pain (if pain is recorded as a health indication), comorbidities, medicinal cannabis type and dosage, date and dose of any previously prescribed medicinal cannabis, recruitment physician ID, and reasons for declining study participation (if applicable).

#### Patient Consent and Demographics

Patients who provide email addresses will receive an email with a link to the patient consent and demographic form corresponding to their study record ID. Patient consent and demographic questions include the following: consent to participate (or opt out), reasons for declining study participation (if applicable), ethnicity and cultural background, education, living arrangements, marital status, height, weight, gender identity, work status, access to health services, any medication other than medicinal cannabis taken during the last 4 weeks for health indication, and previous history of cannabis use.

### PROM Administration

#### Administration

Baseline PROMs will be presented to participants on the web automatically after completing the demographic questions. Participants self-complete the questionnaires through the web-based platform at home, accessible on a computer or other device with an internet connection, depending on their preference. All the questionnaires will be administered in the same order. It is anticipated that completion of baseline questionnaires may take up to 30 minutes. Follow-up questionnaires may take approximately 25 minutes. We have estimated the time to complete the questionnaires (including demographic questions) based on 10-12 seconds per item [57].

#### Patient-Reported Outcome Measures

All participants will complete the following PROMs.

##### Generic HRQL

Generic HRQL will be assessed in all participants using the EuroQol 5-Dimension questionnaire (EQ-5D-5L). The EQ-5D-5L is a standardized measure of health status developed by the EuroQol Group to provide a simple, generic measure of health for clinical and economic appraisals [58]. EQ-5D-5L is designed for self-completion by respondents and consists of 5 items covering the dimensions of mobility, self-care, usual activities, pain or discomfort, and anxiety or depression. Ratings for each item range from 1 (no problem) to 5 (extreme problem), with a recall period of *today*. In addition to the 5 items, there is a visual numeric scale of global health rated on a scale of 0-100. The questionnaire has validated language translations suitable for use in Australia.

To make the EQ-5D-5L suitable for use in economic evaluations, health states were valued using a preference-elicitation method in the general population. Australian national values have been collected and subsequently modeled and will be used for economic analysis [59].

All participants will receive the EORTC QLQ-C30 core quality of life cancer questionnaire [52], which includes core domains of functioning, cancer-specific symptoms, fatigue, and general pain. The QLQ-C30 core questionnaire was designed to be used by any patient participating in a cancer clinical trial; however, it has also been used to evaluate HRQL in other health conditions [60-64], as well as in large general population samples in Europe, the United States, and Australia [65]. It is a 30-item questionnaire with a recall period of 1 week and contains 9 multi-item subscales and 6 single items. It incorporates 5 functional scales (physical, role, cognitive, emotional, and social functioning), 3 symptom scales (fatigue, pain, and nausea or vomiting), and a global health status and HRQL scale. The single items assess dyspnea, appetite loss, sleep disturbance, constipation, diarrhea, and perceived financial impact of disease and treatment. The ratings for each item range from 1 (not at all) to 4 (very much). The QLQ-C30 also produces a summary score of HRQL based on 13 scales [66].

The QLQ-C30 can be used for economic evaluation through the QLU-C10D [67], a health state classification system derived from the QLQ-C30 for which Australian utility weights have been established [68].

##### Overall Change in Health Status

Patients’ subjective rating of overall change in health status related to their primary health condition will be assessed using the Patients’ Global Impression of Change [69]. The Patients’ Global Impression of Change contains 1 item rated from 1 (very much improved) to 7 (very much worse). The recall period is *since beginning medicinal cannabis treatment*.

##### Anxiety and Depression

Anxiety, depression, and stress will be assessed in all participants with the validated 21-item short version of the Depression, Anxiety, and Stress Scale [70]. The Depression, Anxiety, and Stress Scale-21 includes 3 scales, each containing 7 items, assessing depression, anxiety, and stress. The depression scale assesses dysphoria, hopelessness, devaluation of life, self-deprecation, lack of interest or involvement, anhedonia, and inertia. The anxiety scale assesses autonomic arousal, skeletal muscle effects, situational anxiety, and subjective experience of anxious affect. The stress scale assesses difficulty relaxing, nervous arousal, and being easily upset or agitated, irritable or overreactive, and impatient. Ratings for each item range from 0 (not at all) to 3 (very much or most of the time) with a recall period of 1 week [71].

##### Sleep and Fatigue

Sleep quality will be assessed in all participants using the Patient-Reported Outcomes Measurement Information System (PROMIS) Short Form version 1.0: Sleep Disturbance 8b [72]. This measurement system is a universal, rather than disease-specific, 8 item assessment of sleep quality, sleep depth, and restoration associated with sleep. Items are rated from 1 (not at all) to 5 (very much so), with a recall period of 1 week.

Fatigue will be assessed in all participants using the PROMIS Fatigue 13a or the Functional Assessment of Chronic Illness Therapy Fatigue Scale [73]. The 13-item measure has been validated in the general population as well as in patients with cancer, anemia, and arthritis [74,75]. The scale consists of 2 domains: 5 items covering fatigue experience and 8 items assessing the impact of fatigue on daily activities. Ratings for each item range from 0 (not at all) to 4 (very much so), with a recall period of 1 week.

#### Conditional PROMs

The following questionnaires will only be administered to patients with identified conditions or health status.

##### Palliative Care

To reduce the burden on patients with a primary health indication of palliative care for advanced, symptomatic, incurable cancer with a life expectancy of a few months, they will receive the EORTC QLQ-C15-PAL instead of the QLQ-C30. It is a shorter, 15-item questionnaire that assesses the same outcomes as the QLQ-C30 questionnaire and is used extensively in the palliative care setting [76]. Palliative care participants will only complete the EQ-5D and QLQ-C15 questionnaires.

##### Pain

Participants with pain as a health indication in their baseline clinical data will complete additional pain-specific questionnaires (excluding those in palliative care):

Pain intensity will be assessed using the PROMIS Scale version 1.0: Pain Intensity 3a (PS-PI) [77]. The scale includes 3 items assessing pain intensity: 2 items cover pain at its worst, on average, over the last 1 week and 1 item about current pain. All items are rated from 1 (no pain) to 5 (very severe).

Pain interference will be assessed using the PROMIS Short Form version 1.0: Pain Interference 8a [78]. This measurement system contains 8 items measuring the degree to which pain interferes with physical, emotional, and social activities. Items are rated from 1 (not at all) to 5 (very much so), with a recall period of 1 week.

##### Motor Function

Participants with movement disorder, chorea, as a health indication will be assessed with the Quality of Life in Neurological Disorders Short Form version 2.0–Huntington’s Disease health-related Quality of LIFE-Chorea 6a [79]. This 6-item scale producing 1 score was developed for patients with Huntington disease and is appropriate for patients experiencing irregular, random, involuntary movements of varying amplitude affecting the face, trunk, and limbs. The domains cover the impact of movement disorders on physical activity and participation, with each item rated from 1 (never or not at all) to 5 (always or very much), with a recall period of 1 week.

Participants with movement disorders affecting the upper body as a health indication will be assessed using the Quality of Life in Neurological Disorders version 1.0: Upper Extremity Function (Fine Motor and Activities of Daily Living) Short Form [80]. This 8-item scale assesses the ability to perform various activities involving digital, manual, and reach-related functions, ranging from fine motor to self-care (activities of daily living) for patients with stroke, MS, amyotrophic lateral sclerosis, Parkinson disease, epilepsy, and muscular dystrophy. Items are rated from 1 (unable to do) to 5 (without any difficulty) and emphasize current capabilities; therefore, they do not use a recall period.

##### Work Status

For participants who indicate that they are working or would normally be working (ie, not retired or only studying), the impact of health on work performance will be assessed using the absenteeism and presenteeism questions of the World Health Organization’s Health and Work Performance Questionnaire [81]. The questionnaire contains 2 items covering absenteeism in the last 1 week and 2 items covering absenteeism in the last 4 weeks, rated in number of days. Presenteeism is covered by 3 items rated from 0 (worst performance) to 10 (top performance).

#### Follow-Up Data Collection

Participants will receive automatic reminders from the REDCap system to their email addresses at scheduled follow-up assessment time points (Table 1). Follow-up questionnaires can be completed using computers or mobile devices depending on their preference. Up to 2 email reminders to complete the follow-up questionnaires will be sent within the assessment time windows (Table 1). The following questions will be added to the front page of the follow-up questionnaires: current cannabis product and dose, any reduction in other medications taken for health indication because of using medicinal cannabis (including brand, strength, and dose), and work status.

**Table 1 table1:** Patient-reported outcome assessment schedule.

PRO^a^ measure	Baseline	Titration^b^	1-month follow-up	2-month follow-up	3-month follow-up	5-month follow-up	7-month follow-up	9-month follow-up	12-month follow-up
		14-21 days after T0	4 weeks (and 3 days) after T1	8 weeks (and 7 days) after T1	13 weeks (and 7 days) after T1	21 weeks (and 7 days) after T1	30 weeks (and 7 days) after T1	39 weeks (and 7 days) after T1	52 weeks (and 14 days) after T1
	T0	T1	T2	T3	T4	T5	T6	T7	T8
EQ-5D^c^ questionnaire for measuring generic health status	✓	✓	✓	✓	✓	✓	✓	✓	✓
QLQ-C30^d^	✓	✓	✓	✓	✓	✓	✓	✓	✓
Depression, Anxiety, and Stress Scale-21	✓	✓	✓	✓	✓	✓	✓	✓	✓
PROMIS^e^ Short Form for Sleep Disturbance	✓	✓	✓	✓	✓	✓	✓	✓	✓
PROMIS Short Form for Fatigue-Fat	✓	✓	✓	✓	✓	✓	✓	✓	✓
Patients’ Global Impression of Change		✓	✓	✓	✓	✓	✓	✓	✓
World Health Organization Health and Work Performance Questionnaire: Absenteeism and Presenteeism questions	✓		✓		✓		✓		✓
PROMIS Scale for Pain Intensity^f^	✓	✓	✓	✓	✓	✓	✓	✓	✓
PROMIS Short Form for Pain Interference^f^	✓	✓	✓	✓	✓	✓	✓	✓	✓
Neuro-QoL^g^ Short Form for chorea^h^	✓	✓	✓	✓	✓	✓	✓	✓	✓
Neuro-QoL Upper Extremity Function Short Form^h^	✓	✓	✓	✓	✓	✓	✓	✓	✓
15-item version of QLQ-C30 for Palliative Care patients receiving palliative care^i^	✓	✓	✓	✓	✓				

^a^PRO: patient-reported outcome.

^b^The titration period is of approximately 2 weeks. As the EQ-5D assesses the current state (today), whereas the other patient-reported outcome questionnaires have a recall period of the past week, the time period is within 2-3 weeks to capture the end of titration across the questionnaires.

^c^EQ-5D: EuroQol 5-Dimension.

^d^QLQ-C30: Quality of Life Questionnaire, 30 items.

^e^PROMIS: Patient-Reported Outcomes Measurement Information System.

^f^Pain questionnaires will be only administered to participants with a health indication of pain.

^g^Neuro-QoL: Quality of Life in Neurological Disorders.

^h^Impact on Motor Function Questionnaire will be only administered to patients with a health indication of movement disorder.

^i^Participants in palliative care with life expectancy of a few months will only complete the EuroQol 5-Dimension and Quality of Life Questionnaire, 15 items.

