#### Exploratory Objectives

The exploratory objectives of this study are to explore (1) which individuals are more likely to have lower symptom burden and greater HRQL, (2) associations among PROs, with the hypothesis that a high symptom burden is associated with poorer HRQL, and (3) associations between PROs and resource and medication use over time, with the hypothesis that lower symptom burden is associated with reduced health care–resource use and reduced use of opioids and other prescribed medications for managing symptoms.

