#### Economic Evaluation

The economic evaluation will use collected data around pharmaceutical and other medical costs to explore the drivers of patient-level costs. As this study is not a comparative randomized trial, we are not proposing to conduct a formal economic evaluation, resulting in a cost per quality-adjusted life year. We will instead use baseline resource use as an indicator of typical care and contrast resource use throughout the study with baseline data. We will explore the relationship between HRQL and resource use across the cohort, which is potentially important information for future economic evaluation of medicinal cannabis.

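### Follow-up records other medication only as reductions credited to cannabis and lists no measure of health service use, so exploratory objective 3 and the resource-use contrast are only partly supported

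*Protocol article*

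**What the plan says.** Exploratory objective 3 (Exploratory Objectives) is to study "associations between PROs and resource and medication use over time". The section also states what the study expects to find: "lower symptom burden is associated with reduced health care–resource use and reduced use of opioids and other prescribed medications for managing symptoms". The Economic Evaluation section plans to "use baseline resource use as an indicator of typical care and contrast resource use throughout the study with baseline data". It adds: "The economic evaluation will use collected data around pharmaceutical and other medical costs to explore the drivers of patient-level costs". It does not say where those data come from.

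On collection, the baseline form (Patient Consent and Demographics) covers "access to health services, any medication other than medicinal cannabis taken during the last 4 weeks for health indication". The section Follow-Up Data Collection lists what is put on the front page of each later questionnaire: current cannabis product and dose, then "any reduction in other medications taken for health indication because of using medicinal cannabis (including brand, strength, and dose), and work status". Table 1 adds the patient-reported outcome measures and the absenteeism and presenteeism questions. The data entered by physicians are screening and registration data.

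**The concern.** An analysis of medication and resource use over time needs the same quantity measured the same way at baseline and later. Here the baseline question on medication is neutral and complete. The follow-up question looks in one direction and asks the patient to name the cause. Health services appear at baseline and then drop out of the listed items.

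Two results are at stake. A statement about opioid or other medication use during treatment would rest on an item that can register a fall but not a rise. Patients who feel better may also be readier to credit cannabis for a reduction, which could strengthen the very association that objective 3 expects; this is plausible but cannot be shown from the document. The contrast of resource use with baseline would have nothing on the listed follow-up forms to contrast.

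There is also an indirect effect. This is a cohort without a control group, and a newly started or increased symptom treatment is one alternative explanation for a better score. The listed follow-up items would not reveal it.

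**Working it through.** The plan gives no figure on this point, so there is none to reproduce. The check sets what the analyses need against what the listed forms collect.

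| Quantity | Baseline | Follow-up (T1 to T8) | What can be derived |
|---|---|---|---|
| Other medication for the indication | All, past 4 weeks | Reductions credited to cannabis, with brand, strength and dose | Reduction reported or not; no net change |
| Health services | One item, described as access | None listed | No within-patient contrast |
| Cannabis product and dose | Yes, entered by the physician | Yes | Followed over time |
| Work performance | Absenteeism and presenteeism | T2, T4, T6, T8 | Productivity, not service use |

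**Medication.** Take five things that can happen to a patient's other medication, and the answer that the follow-up item, as described, would give:

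1. Reduced, and the patient credits cannabis: reduction.
2. Reduced for another reason: no reduction.
3. Unchanged: no reduction.
4. Dose of an existing drug raised: no reduction.
5. New drug started: no reduction.

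Four of the five share one answer. A patient who cuts one drug and starts another is recorded only as having reduced.

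**Illustration of net change.** The shares are assumed, not taken from the document, and every reduction is assumed to be credited to cannabis. Net change is the share reducing minus the share increasing.

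- 20% reduce, 20% increase: true net = 20 − 20 = 0 percentage points; the form shows 20% reduced and 0% increased.
- 30% reduce, 10% increase: true net = 30 − 10 = 20 percentage points; the form shows 30% reduced and 0% increased.

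This concerns change in the cohort as a whole. It does not measure any bias in the association between symptom burden and medication use.

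**Health services.** Listed items: 1 at T0, and 0 at the 8 follow-ups. No record linkage and no clinician follow-up form is described.

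**Room to change, at the article's data cut.** By June 4, 2021, 833 of 2142 participants had completed baseline, which leaves 2142 − 833 = 1309, or 1309/2142 = 61%. Recruitment had run since November 27, 2020, that is 189 days or 27 weeks. T6 falls 30 weeks after T1, and T1 is at least 2 weeks after T0, so T6 comes no earlier than week 32. No participant had then reached T6, T7 or T8.

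**The case against.** Several points on the other side stand.

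- A reader might infer that the form itself confirms the hypothesis. It does not. Objective 3 states an association between symptom burden and medication use. A reduced or not-reduced answer varies between patients and may be related to symptom burden in either direction or not at all, so the hypothesis can fail.
- A reader might infer that objective 3 cannot be answered at all, or that a stable patient cannot be recorded. Neither follows. A patient can report no reduction, and reductions come with brand, strength and dose, so a limited one-sided analysis is possible. What is lost is the distinction between no change, an increase, and a reduction for another reason.
- A reader might infer that no resource-use data exist after baseline. The article is a condensed account, the forms are not shown, and the Economic Evaluation section refers to collected cost data. A source may exist that the article does not name. The supportable statement is that none is stated.
- The baseline item is described as access to health services. If it asks about access and not use, simply repeating it would not supply the contrast.
- Only an exploratory objective is involved, and the economic section itself disclaims a formal evaluation.

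The reply that such detail belongs in the analysis plan or full protocol does not remove the medication point. The article states the content of the follow-up question, and no analysis plan can recover increases that were never asked about.

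**Conclusion.** The concern holds in a limited form. As listed, the follow-up items capture other medication only as patient-attributed reductions. Increases, new drugs and reductions for other reasons are missed, net change from baseline cannot be derived, and the medication part of exploratory objective 3 can be examined only one-sidedly. This part is firm and rests on the stated content of the question.

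The resource-use part of objective 3 and the contrast under Economic Evaluation have no stated follow-up source. This part is less certain, because it assumes that the listed items are all that is collected.

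The size of any distortion cannot be computed from the document. Severity is moderate: the primary and secondary objectives and the three formal hypotheses are not directly affected.

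**What to change.** 1. **Medication.** At follow-up, replace the attributed-reduction item with the neutral 4-week question used at baseline, or add that question beside it. Derive increases, decreases, starts and stops from the difference. The article does not say that the baseline item records strength and dose; if it does not, add them there too, or dose changes cannot be derived. At T1, 14 to 21 days after T0, a 4-week (28-day) window reaches back 28 − 21 = 7 to 28 − 14 = 14 days before baseline, so base the comparison on T2 onwards.
2. **Health services.** Add an item on use of services, asked identically at baseline and follow-up, or name the data source that the Economic Evaluation section relies on. If such a source exists, naming it settles this half.
3. **Data already collected.** Label the outcome as patient-attributed reduction, report it as such, and narrow objective 3 and the Economic Evaluation text to match.

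Cost: a change to the REDCap forms and an ethics notification. The plan's own estimate is 10 to 12 seconds per item, but a full medication list with strength and dose takes longer than one item, on forms that already take about 25 minutes. Participants already enrolled will lack the neutral item at past visits, so the series is split and the date of the form change has to be carried into the analysis.
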